#### Food frequency questionnaire (FFQ) [66]

An abbreviated online version of a validated complementary feeding food frequency questionnaire for mothers to complete in about 15 min when infants are 9, 12, and 24 months old collects data on infants’ vegetable intake and variety. The questionnaire is abbreviated because only items relating to vegetables, fruit, and meat and alternatives are included to meet study objectives and reduce participant burden. Additional items relating to milk feeding history are added for the purpose of this study. The tool asks mothers to enter the total number of times and typical amount of a specified food (e.g. “Beans and peas”) eaten by the infant in the last 4 days using free text. Check boxes are used for milk feeding items. The data will be interpreted so that the greater variety and frequency of a vegetable observed, the greater intake of that vegetable. As the tool is validated to assess nutrient intake in infants, this data may be useful for further analysis of nutrient intakes when following a “vegetables first” approach to complementary feeding.

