**Methods/design:**

One-hundred and twenty mother-infant pairs living in Auckland, New Zealand, will be randomised to receive either vegetables only (intervention) or fruit and vegetables (control) for 28 days, starting from the first day of complementary feeding at around 4–6 months of age. Infants will be presented with a brassica (broccoli), followed by a green leafy vegetable (spinach) and sweet fruit (pear) at 9 months of age. The primary outcome measures of intake of each food will be assessed using a weighed food diary. Secondary outcome measures of overall intake, liking and wanting of vegetables will be assessed using a food frequency questionnaire, liking tool and video coding tool, respectively, at 9, 12, and 24 months of age. Infant growth and iron status will be assessed as part of health screening and monitoring at baseline, post intervention and 9 months of age. Other biological samples to be collected include infant stool samples, vitamin D (mother and infant), iron status (mother), and mothers’ diet.

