### Data collection

Mothers will be emailed the links to the online demographics, baby behaviour, and pregnancy/lactation food frequency questionnaires to complete at home before their first visit to the HNRU at which other baseline data (infant anthropometry and blood samples) will be collected. The 4-week intervention and primary data collection (mother reported infant vegetable liking and intake, video-recorded meals) will take place in the infant’s home environment from May 2019 to October 2021. Follow-up data (anthropometry and/or blood samples) will be collected at 9, 12, and 24 months of age at the HNRU; home visits will be available as required. In the instance where visits are not possible, mothers will be asked to provide current infant growth measurements (following standardised instructions given by the researcher) and food diaries by email or post. Virtual meetings using Zoom or Skype will be available for additional support. Additional child vegetable/fruit liking and food frequency questionnaires will be completed by mothers at home when their infant is 9, 12, and 24 months old. To the extent possible, we will continue to collect data for all outcome measures for participants who discontinue or deviate from the intervention protocols, while anticipating and planning for missing data. Given the potential for this cohort to provide valuable data for future early life nutrition research, additional outcome measures will be collected. These include mothers’ iron status/vitamin D status (at baseline), infants’ vitamin D status (at baseline), and infant stool samples for microbiota analysis (pre- and post-4-week intervention, and all follow-ups). Such data may be useful to assess maternal iron status 6 months post-partum or infant vitamin D status and links to the microbiome. Table 2 outlines the primary study outcome measures and testing methods. Figure 3 provides the schedule of enrolment, intervention, and assessment.

**Table 2 Tab2:** Summary of the study outcome measures and methods

Variables	Method
Primary outcomes	
Vegetable liking	Liking tool (Appendix A). Completed by mother at home
	Rate of acceptance video coding tool. Mother video-records meals. Independent researcher codes infant behaviours
	Child vegetable and fruit liking questionnaires. Completed online by mother
Vegetable intake	Weighed food diary. Completed by mothers at home
	FFQ. Completed online by mother
Blood analysis^a^	

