### Weighed food diary

Mothers will complete a 4-day weighed food diary during the first and last 4 days of the 4-week intervention to primarily measure infant food intake (grammes). In alignment with other studies [33–39, 55–57], this will involve weighing the food before and after consumption using provided digital scales and completing the food record sheet. Estimated spills or food fallen on the bib will be recorded. The greater amount of food eaten may indicate a greater preference or acceptance for that food. In addition, the diary collects data for breast/formula milk feeding, meat consumption, and medication/supplements. Mothers can report factors that may have affected infant feeding each day (e.g. teething, unwell).

The diary is designed specifically for this study and includes a liking tool to assess the degree that infants like the study foods (see Liking tool). Combining these tools into one booklet should reduce participant burden and improve data collection. Detailed and visually appealing instructions on the feeding environment and protocol, such as food rotation and video-recorded meals, are included. Food diaries for each group differ only by the allocated foods mentioned; for example, instructions for the orange food do not feature for the intervention group diary. Week 1 and week 4 diaries also differ slightly by the removal of irrelevant instructions; for example, the week 4 diary excludes the instruction “After the first four days…”. A similar 3-day weighed food diary will be provided at 9 months of age but includes the option to list any other vegetables or fruits eaten that day.

Weighed food records are considered the best estimate food intake for children aged 0.5 to 4 years [58]. The use of 4- and 3-day weighed food diaries should help to reduce participant burden that is typically associated with those of greater durations (e.g. a 7-day food diary) without compromising accuracy [59, 60]. These durations also fit well with the protocol; for example, three tests meals offered over three consecutive days at 9 months of age is appropriately measured by a 3-day food diary.

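### The FFQ rule reads vegetable intake from variety and frequency and leaves out the amount eaten, although the FFQ is the only intake measure described at 12 and 24 months

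*Protocol article*

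**What the plan says.** The FFQ section of the protocol article describes an abbreviated form of a validated questionnaire, completed by mothers. On content: "The tool asks mothers to enter the total number of times and typical amount of a specified food", counted as eaten by the infant over the last 4 days. On timing and purpose, it is completed "when infants are 9, 12, and 24 months old collects data on infants’ vegetable intake and variety", so intake and variety are named as two things. The rule for reading the answers follows: "The data will be interpreted so that the greater variety and frequency of a vegetable observed, the greater intake of that vegetable". The section adds that the data may later serve an analysis of nutrient intakes.

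The abstract gives the FFQ its role: "Secondary outcome measures of overall intake, liking and wanting of vegetables will be assessed using a food frequency questionnaire". Overall intake is the item in that list that belongs to the FFQ, and the ages given are 9, 12 and 24 months.

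The weighed diary has a different schedule. During the intervention: "Mothers will complete a 4-day weighed food diary during the first and last 4 days of the 4-week intervention". Afterwards: "A similar 3-day weighed food diary will be provided at 9 months of age". The article describes no diary at 12 or 24 months.

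**The concern.** The hypothesis is about later intake of vegetables, and elsewhere the article treats intake as grams: the sample size rests on a difference in grams, and the diary weighs food before and after the meal. The FFQ collects what is needed to approximate grams, but the rule stated for it names only variety and frequency.

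Two things follow. First, if infants in one arm eat vegetables as often as those in the other but take larger portions, the stated rule shows no difference. Larger portions are one plausible form of better acceptance; the Weighed food diary section itself takes a larger amount eaten as a possible sign of preference. Second, variety is a property of the whole diet. It cannot indicate how much of one particular vegetable was eaten, so the rule merges two quantities that the same section lists separately.

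At stake is the reading of the 12- and 24-month results. The Background notes that earlier work suggested higher daily consumption to at least 12 months and left open whether the effect could be kept to 24 months. This trial's evidence on intake at those ages comes from the FFQ.

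**Working it through.** The point concerns an outcome definition, and the plan gives no figure to reproduce for it. The check has three steps.

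**1. Which intake instrument is used when** (Weighed food diary, Data collection and FFQ sections)

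| Time | Weighed diary | FFQ |
|---|---|---|
| First and last 4 days of the intervention | yes | no |
| 9 months | yes (3 days) | yes |
| 12 months | none described | yes |
| 24 months | none described | yes |

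The Data collection section confirms the FFQ ages: "food frequency questionnaires will be completed by mothers at home when their infant is 9, 12, and 24 months old". It also says that where visits are not possible, mothers will be asked for growth measurements and "food diaries by email or post". That is a fallback route of delivery. It does not set up a diary at 12 or 24 months.

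**2. Fields collected against the rule stated**

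- Times eaten in 4 days: collected, in the rule (frequency).
- Typical amount: collected, not in the rule.
- Number of different vegetables: can be derived, and is in the rule (variety), but applied to intake of one vegetable.

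The collected fields give intake directly: g/day = times × typical amount / 4.

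**3. What the omission can do** (all values below are assumptions; the documents give no portion sizes or frequencies)

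*Same frequency, different portions.* Six times at 15 g: 6 × 15 / 4 = 22.5 g/day. Six times at 25 g: 6 × 25 / 4 = 37.5 g/day. The difference of 15 g/day is invisible to frequency.

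*Reversed ranking.* Eight times at 10 g: 8 × 10 / 4 = 20 g/day. Four times at 30 g: 4 × 30 / 4 = 30 g/day. Frequency ranks the first infant higher; grams rank the second higher.

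*How good a proxy is frequency?* Let the count f in 4 days have mean 6 and variance 15 (a Poisson count whose rate follows a gamma distribution with mean 6 and shape 4: 6 + 36/4 = 15). Let portion size be independent of f with coefficient of variation c. Then E(f²) = 15 + 36 = 51, and the correlation of f with grams per day is √[15 / (15 + 51c²)].

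| c | 15 + 51c² | Correlation, formula | Correlation, simulation |
|---|---|---|---|
| 0.25 | 18.19 | 0.91 | 0.91 |
| 0.50 | 27.75 | 0.74 | 0.74 |
| 0.75 | 43.69 | 0.59 | 0.58 |
| 1.00 | 66.00 | 0.48 | 0.47 |

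The simulation used 200,000 infants and log-normal portions. Frequency is a good proxy if portions vary little and a weak one if they vary a lot. The correlation within a group does not settle the comparison between arms: for a given distribution of frequency, a shift in portion size in one arm leaves the frequency comparison unchanged, whatever c is.

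**The case against.** The strongest reply is that the sentence is a remark on direction, like the article's remarks that more food eaten or more positive behaviours suggest greater liking, and not a derivation formula. The Statistical analysis section defines no FFQ variable, and a conversion to g/day would normally sit in a fuller document. Part of this stands: the absence of a formula from a condensed article is no fault. But the article does more than stay silent. It states how the answers are to be read as intake, and that statement names variety and frequency and leaves out an amount collected by the same tool.

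A reader might go further in four ways that the documents do not support.

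- *That the amounts will be discarded.* The text omits them from the rule but does not say so, and the possible nutrient analysis would need them.
- *That the FFQ would not measure intake at all.* Frequency of eating is a partial proxy, and under some assumptions above a close one. What it does not capture is the amount eaten.
- *That frequency mainly reflects what mothers offer.* The tool counts times eaten by the infant. Eating is limited by what is offered, but that applies to reported grams as well.
- *That the trial's main result is affected.* The Methods/design section sets the primary endpoint as vegetable intake at 9 months, and the abstract measures it by weighed diary. Table 2 does list the FFQ under primary outcomes, but weighed grams exist at that age and do not depend on the FFQ rule.

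It is also fair to say that two hypothetical infants show only that rankings can reverse. They do not estimate bias between randomised arms.

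**Conclusion.** The point holds for the FFQ intake outcome. The stated rule infers intake from variety and frequency alone, leaves out an amount that is collected, and confuses variety across vegetables with intake of one vegetable. The consequence is greatest at 12 and 24 months, where no other intake measure is described and where the rule could not show a between-arm difference in portion size.

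The size cannot be fixed from the documents. Under the assumptions above (mean of 6 occasions in 4 days, portion size independent of frequency), the correlation of frequency with grams per day lies between about 0.91 and 0.48 for a portion-size coefficient of variation from 0.25 to 1.0. If infants who eat vegetables more often also take larger portions, frequency would do better than this; if they take smaller ones, worse. The weighed-diary endpoint at 9 months stands as planned. Because the amounts are already requested, no information need be lost, and the matter should be settled before the follow-up data are analysed.

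**What to change.** Replace the interpretive sentence in the FFQ section with a definition:

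- FFQ vegetable intake (g/day) = sum over vegetable items of (times eaten in the last 4 days × typical amount in grams) / 4, analysed as the secondary intake outcome at 9, 12 and 24 months.
- Frequency (times eaten) and variety (number of different vegetables eaten) reported as separate outcomes, neither described as intake.

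Fixing this before analysis also prevents a choice among grams, frequency and variety once results are known.

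**Cost.** Mothers answer nothing new. Free-text amounts must be coded to grams, which needs a written conversion table with a rule for amounts that cannot be coded. Since the article says researchers are not blinded after assignment, the coding is best done without sight of the arm. Portions reported by mothers add some measurement error, which is the reason to keep frequency alongside as a supporting outcome.

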#### Fruit and vegetable liking questionnaire

An online child vegetable and fruit liking questionnaire for mothers to complete when infants are 9, 12, and 24 months old collects data on vegetables and fruits tried and liked. It features visually appealing images and the same liking scale used in the adapted infant liking tool. Scores of 4 or above indicate a greater liking for the food. Content validity is confirmed by four experts in the nutrition and dietetic field and five mothers not participating in the study. To improve completion, the questionnaire is divided into two online questionnaires, with one focusing on vegetables and the other on fruit; the estimated completion time is 10 min each.

#### Baby Eating Behaviour Questionnaire (BEBQ)

As infant feeding behaviour characteristics could impact results, an online version of the validated BEBQ is to be completed [54]. This is an 18-item questionnaire with 17 items measuring four aspects of infant feeding behaviour and one item measuring general appetite before starting complementary feeding. Response options range from never = 1 to always = 5. Scoring involves calculating mean scores for each subscale with higher mean scores indicating greater presence of the feeding behaviour. The four themes are enjoyment of food (e.g. My baby seems contented while feeding), food responsiveness (e.g. My baby frequently wants more milk than I provide), slowness in eating (e.g. My baby takes more than 30 min to finish feeding), and satiety responsiveness (e.g. My baby get full up easily). This questionnaire should take 10 min to complete. It is expected that infants who enjoy food less, are less food responsive, eat slower, are less sensitive to internal cues of satiety, and have a smaller overall appetite may be more difficult to feed and perhaps less willing to accept vegetables specifically, compared to infants with the opposite traits.

### Compliance to study protocol

A 2-min check-in compliance questionnaire collects data on how many days the intervention food was offered, other food or drink consumed other than provided in the study, medications, and factors that may affect infant feeding (e.g. teething). This will be emailed to participants on the completion of each intervention week. Mothers will be contacted by email or telephone at 9-, 12- and 24-month follow-ups and an e-card will be sent on child birthdays to improve sample retention. Mothers will receive a personalised baby bag, kitchen scales, visually appealing infant feeding resources, and petrol vouchers at no cost to them in order to improve participation rates. The video footage from mothers’ first video recordings will be checked for compliance and quality, with corrections (e.g. lighting, camera angle, environment) administered by the researcher as required.

### Website

A study website is designed for participants to use when wishing to register, complete the eligibility questionnaire, learn more about the study, contact the researchers, and access exclusive infant resources. The use of a New Zealand website domain, the Massey University logo, and a visually appealing study banner may improve credibility and recruitment. The website acts as a platform for distributing participant education and resources, including seven videos, three downloadable fridge magnets, a food safety flyer, and three meat purée recipe cards with accompanying videos. These are based on Ministry of Health infant feeding guidelines and created using design software (Canva, Photoshop, and Adobe Premier Pro). Images and video content are obtained from a photography/video shoot with written consent from the participating subjects, purchased from Shutterstock® or taken from Creative Commons. Using online surveys, each infant feeding resource is peer-reviewed by six experts in infant nutrition and 20 mothers. Feedback informed revisions; for example, it was recommended to use brighter colours for the recipe cards to improve engagement.

### Adverse events

In the rare case that an allergic reaction to the infant foods, participants will be instructed to stop feeding the food and may withdraw from the trial and provided a referral to a doctor. Reports of gastrointestinal symptoms or other side effects will be further investigated by the trial registered Dietitian and the infant’s health will be monitored closely for the duration of the intervention. If the adverse event persists, withdrawal from the trial and/or a referral to a doctor for further investigation is expected. All adverse events will be recorded, and mothers offered telephone/email support. If the participant needs to make a claim to Accident Compensation Corporation (ACC) due to an adverse event and the claim is not accepted, then the researcher will initiate processes to ensure they receive appropriate compensation.

### Blood sampling, stool collection, and analysis

As part of screening for and monitoring infant health and iron status, capillary blood samples will be taken from infants by a registered phlebotomist using a standard “heel prick” test at baseline, after the intervention, and at the 9-month follow-up. The focus on monitoring iron status reflects concerns for meeting iron requirements during the complementary feeding period [24], with iron deficiency having consequences that are more serious and irreversible than in adults [1, 67]. Thus, serum will be used for the analysis of serum ferritin and C-reactive protein (CRP) at LabTests (Auckland). Haemoglobin will be measured using HemoCue in our HNRU laboratory. If Haemoglobin is <110 g/L, the participant will be notified and given a referral letter to see their doctor.

Additional blood and stool collection will be taken in the interest of future research. At baseline, venous blood samples will be collected from mothers and will be stored for later analysis of iron and vitamin D. Whatman cards will collect infant serum for a future study investigating infant vitamin D at baseline. For microbiome research purposes, mothers will collect a stool sample from their infant before and after the 4-week intervention, then at 9, 12, and 24 months of age.

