Infant iron studies^b^	“Heel prick” test by phlebotomist at Massey University or home
Infant vitamin D	“Heel prick” test by phlebotomist at Massey University or home using *Whatman card*
Mother iron/vitamin D	Venous blood sample collection by phlebotomist at Massey University
Other measures	
Infant anthropometry	Head circumference: paper measuring tape, widest part of head, three measures, select largest measurement to the nearest 0.1 cm; length: infant length board; weight: infant electronic weighing scales, no nappy; measured by researcher at Massey University or participant home
Demographics	Completed online by mother
Mother diet	Pregnancy and lactation FFQ and FCQ. Completed online by mother
Baby eating behaviour	Baby eating behaviour questionnaire [54]. Completed online by mother
Compliance	2-min check-in questionnaires. Completed online by mother

^a^Analysed by LabTests, Auckland

^b^Serum ferritin, C-reactive protein (CRP), haemoglobin

*FFQ* food frequency questionnaire, *FFQ* food frequency questionnaire, *FCQ* food choices questionnaire

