### Dissemination of results

During each visit, mothers will receive their infant’s growth measurements and blood haemoglobin result. The remaining blood results will be provided on request. Once available, participants who completed the intervention will receive a summary of findings in lay language, and whether they were assigned to the intervention or control. Results will be presented at national and international scientific conferences, prepared for publication in peer-reviewed journals, and circulated to the media and should be of interest to a range of audiences including families, health professionals, district health boards, academics, and primary health organisations. Individuals with substantive contributions to the design, conduct, interpretation, and reporting of the study will be recognised by granting authorship on the final relevant report.

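### Infant ferritin is measured to monitor iron status, but only haemoglobin below 110 g/L leads to a stated action

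*Protocol article*

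**What the plan says.** The abstract of the protocol article states the purpose of the infant iron measurements: "Infant growth and iron status will be assessed as part of health screening and monitoring at baseline, post intervention and 9 months of age". The section Blood sampling, stool collection, and analysis repeats it: "As part of screening for and monitoring infant health and iron status, capillary blood samples will be taken from infants", at the same three time points. It explains the focus on iron by saying that deficiency does graver and less reversible harm in infants than in adults, and continues: "Thus, serum will be used for the analysis of serum ferritin and C-reactive protein (CRP) at LabTests (Auckland"). Haemoglobin is measured by HemoCue in the study unit. The footnote to Table 2 (Data collection) defines the infant iron studies as "Serum ferritin, C-reactive protein (CRP), haemoglobin".

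One action rule follows: "If Haemoglobin is <110 g/L, the participant will be notified and given a referral letter to see their doctor".

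Samples for other purposes come in a separate paragraph that opens "Additional blood and stool collection will be taken in the interest of future research". It covers maternal blood, infant vitamin D and stool. Infant ferritin and CRP are not in it.

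Dissemination of results says that at each visit mothers receive their infant's "growth measurements and blood haemoglobin result", and then: "The remaining blood results will be provided on request".

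**The concern.** The stated purpose and the stated action do not match. The article names iron deficiency as the risk and presents the ferritin and CRP assays as its response, but it then acts on haemoglobin alone and leaves the other blood results to the mother's request. A ferritin result can be low while haemoglobin is still at or above the threshold. In that case the study holds the finding it set out to look for and has no stated route for it to reach the mother or her doctor.

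What is at stake is the care of individual infants in a trial whose supplied foods are all fruit or vegetables (Table 1). The comparison of vegetable intake at 9 months is not affected.

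**Working it through.** The article gives no figure to reproduce here, so the check sets its provisions side by side.

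**Action rules by analyte** (Table 2 footnote; Blood sampling, stool collection, and analysis; Dissemination of results)

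| Infant analyte | Measured to monitor iron status | Threshold and action stated | Return to mother |
|---|---|---|---|
| Haemoglobin | yes | below 110 g/L: notification and referral letter | at each visit |
| Ferritin | yes | none | on request |
| CRP | yes | none | on request |

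So 1 of 3 analytes has a rule. CRP is there mainly to interpret ferritin, so the substantive gap is a single missing rule, for ferritin.

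**What happens to each infant if the text is followed as written**

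| Haemoglobin | Ferritin | Stated consequence |
|---|---|---|
| below 110 g/L | any | notified and referred |
| 110 g/L or more | low | none; value disclosed only if the mother asks |
| 110 g/L or more | normal | none needed |

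The middle row is the gap.

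**Could another provision close it?**

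- Adverse events: acts on allergic reactions, gastrointestinal symptoms and other side effects. No laboratory value is a trigger.
- Infant foods and Website: encouragement to give the family's own meat, with recipe cards and videos. This is general advice, independent of any result. Feeding protocol withholds meat for the first 4 days.
- Education session: an iron pamphlet for all mothers after the intervention. Also independent of any result.
- Later haemoglobin checks: these lead to referral only once haemoglobin has fallen below 110 g/L.

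**How far apart are the haemoglobin checks?** Assume that the post-intervention draw is on day 28 and that feeding starts at 4 to 6 months of age.

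- Baseline to post-intervention: 28 / 30.44 = 0.92 months.
- Age at the post-intervention draw: 4 + 0.92 = 4.92 to 6 + 0.92 = 6.92 months.
- Gap to the 9-month draw: 9 − 4.92 = 4.08 down to 9 − 6.92 = 2.08 months.

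The 9-month draw is the last infant iron draw listed. Data collection mentions possible blood samples at 12 and 24 months but specifies no iron test then, so a low ferritin found at 9 months has no stated recheck.

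**Scale.** The abstract gives 120 pairs; Participants gives 65 per arm, 2 × 65 = 130. Each 1% of infants in the gap is therefore 1.2 to 1.3 infants. This is a conversion only. The actual percentage is unknown, because the article gives no ferritin cut-off and no expected share with low ferritin and haemoglobin of 110 g/L or more.

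**The case against.** The strongest reply is that this is silence in a condensed article. Alert limits and the handling of abnormal results often sit in a full protocol or clinical procedures, and staff may well act on a low ferritin unprompted. On this reading the on-request sentence, under Dissemination of results, governs only copies of results and is no rule on clinical action. The split may be practical: haemoglobin is read in the unit, while ferritin and CRP go to an outside laboratory. The infants are also low risk (term, normal growth, no known disease), the restricted feeding lasts 28 days, meat is encouraged after the first 4 days, haemoglobin is checked three times, and the number affected cannot be estimated.

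Part of this stands. An unseen document could hold a ferritin rule, nothing in the article forbids staff from acting, the magnitude is unknown, and counting CRP as a separate gap adds little.

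The main argument does not carry. The article does not leave result handling elsewhere: it gives a threshold, a notification step, a referral letter and a release policy, and the release policy leaves the results other than haemoglobin to the mother's request. Use of an outside laboratory explains why ferritin is not available at the visit, but not why a low value prompts nothing when it arrives. The remaining safeguards lessen the risk, but none responds to a ferritin value.

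**Conclusion.** The concern holds. As written, low ferritin with haemoglobin of 110 g/L or more leads to no stated notification or referral at any of the three draws, and the mother learns of it only by asking. This conflicts with the stated purpose of monitoring iron status and with the article's reason for doing so.

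The size is one missing action rule, with an unknown number of infants behind it. The conclusion rests on the article's text and assumes that no separate safety plan supplies the rule, so confidence is medium. It should be corrected because it concerns participant safety and costs little; it does not threaten the primary result.

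**What to change.** Amend Blood sampling, stool collection, and analysis and Dissemination of results to state that:

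- existing study staff review infant ferritin and CRP results on receipt;
- a low ferritin, by a cut-off that takes CRP into account and is set in advance by the study's clinicians, triggers the same notification and referral letter as low haemoglobin, without the mother having to ask;
- any iron treatment that follows is recorded and reported by arm.

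The cost is low. The draws, assays and letter already exist. What is added is one agreed cut-off, a little staff time per result and a few extra letters. The drawback is that iron treatment between draws could alter later iron values, which is why it must be recorded by arm. Blinding is not weakened: a ferritin value does not tell a mother which foods she was allocated, and the researchers are already unblinded (Randomisation, blinding, and concealed allocation). If a ferritin rule already exists in another study document, one sentence citing it would be enough.
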